#### Survey

All Guiding Coalition members at each system (*n* = 8 x ~ 15 members = 120) will be invited to participate in a survey using a novel instrument drawn from previously validated scales (Additional File 3) [28], which includes 30 items within 4 domains: learning and problem solving, senior leadership support, structures and processes that support change, and psychological safety. Example item: “*We have goals and metrics in place to guide our efforts to reduce racial inequities in care of patients with sepsis.*” Responses will be entered using the sliding bar function in Qualtrics, with anchors “never” to “always.” To ensure that our instrument captures new concepts related to anti-racist practice, we will conduct cognitive interviews [70, 71] (*n* = 8–10) with respondents similar to Guiding Coalition members, and revise our draft instrument as needed [28, 72–75]. Participants will complete the secure, web-based survey at the launch, midpoint and end of the intervention. To assess changes in 4 domains of organizational culture and overall, we will use hierarchical generalized linear modeling to estimate the association between mean scores and time, accounting for clustering of individual respondents within systems. We will use statistical analysis to determine significant changes at the level *p* < 0.05 for overall culture and each of the 4 domains for each system and the full sample. Analyses will be conducted using SAS V.9.4 and independently corroborated by two analysts. In addition to assessing the impact of the intervention in this study, the survey will be the first (to our knowledge) to measure aspects of organizational culture required for anti-racist systems change.

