Integration will be accomplished through merging in a mixed methods matrix [69, 87] at the final stage of analysis (Additional File: 1 Supplemental Fig. 4). For each site, we will integrate quantitative trend data (overall and by each domain of the survey) and qualitative data. We will classify each site as having positive or no change based on meeting either quantitative (statistically significant change in overall readiness score from baseline to follow up) or qualitative criteria (marked shift in culture characterized by substantial, consistent, specific illustrations of notable changes in three to four of the domains of culture and little to no disconfirming evidence). We will use comparative analysis to describe differences between the systems that achieve substantial change and those that do not. Finally, we will examine differences in clinical outcomes as described in Aim 3 below. Note: analysts will be blinded to all clinical outcomes data during this analysis.

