
#### Analytic approach

We will conduct a comparative interrupted times series (ITS) analysis to examine the relation between the intervention and racial/ethnic differences in sepsis clinical outcomes between AA/B and NHW patients and between LatinX and NHWs. The analysis will be performed separately for our three key outcomes: 1) time to antibiotics, 2) in-hospital mortality, and 30-day readmission and stratified by response to the intervention (change/no change) (Additional File 1; Supplemental Fig. 5). We will consider a pre-exposure to the intervention time beginning 2.5 years (10 quarters) prior to starting the intervention and a postexposure period comprising 2.5 years (10 quarters) following the start of the intervention, with estimates made at every calendar quarter. ITS will be utilized to determine the difference in quarterly rates over time between changers (systems that responded to the intervention) and non-changers, health systems that did not respond to the intervention. Subsequently, ITS allows us to detect if an intervention has impact above and beyond secular trends when randomization is not a feasible option, and is ideal for evaluation of data collected across multiple equally spread time points by testing the changes in the slope of an outcome over time [96]. Additionally, ITS requires at least eight observations pre and post intervention [97]. We will utilize generalized mixed effect models in conjunction with segmented regression to evaluate the effectiveness of our intervention [98]. The model will control for patient-level characteristics, including age, sex, insurance status, Charlson Comorbidity index, and admission through the Emergency Department or transfer from another acute care facility, and hospital-level characteristics including size, academic vs community hospital, number of intensive care beds, annual sepsis case volume. We will also account for seasonality based on calendar quarter by including a “season” term alone and interacted with the treatment indicator and will assess for any residual autocorrelation using autoregressive integrated moving average (ARIMA). To allow a marginal interpretation of results, we will use a linear probability model for all analyses. Because outcomes of patients within a hospital are expected to be correlated, we will account for these non-standard variance–covariance structures by clustering at the hospital level. All coefficients will be modeled as fixed effects.

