## Discussion

To our knowledge this is the first study to evaluate the impact of cultural change on racial inequities in care for patients with sepsis. Aligned with NIH and NIGMS priorities, the results of this study are expected to: 1) further the nascent scientific literature on conceptualizing and measuring structural racism and health outcomes, 2) generate community-driven innovations in sepsis care for dissemination through national organizations such as American College of Chest Physicians, and 3) provide much-needed evidence to inform local and national dialogue around structural racism and health. We fully recognize this study is an audacious proposition. It not only addresses a highly sensitive topic (structural racism), but it also seeks to make measurable change in the structural root causes of inequities in sepsis care. Importantly, we have balanced our ambitions for whole system change with careful operationalization of core constructs and detailed measurement approaches to understand the mechanisms of change. Further, the proposed study may be especially audacious in the context of COVID-19, which will likely strain organizational capacity to participate in change initiatives and is expected to change patient care processes and outcomes. As described above, a period of systematic stakeholder engagement will allow us to adapt the intervention for feasibility in the ever-changing context of COVID-19. Further, given the well-document impact of the pandemic in exposing structural racism and exacerbating racial inequities, the proposed study is both timely and urgent.

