We have anticipated several potential limitations in the proposed methodology. First, to mitigate social desirability bias (participants reporting socially acceptable, rather than authentic, responses) [99], we will use established techniques including attention to our own positionality and engagement of a diverse research team, engagement of a wide range of key informants across the project, use of interview guides with scripted probes to elicit details that would be difficult to misrepresent, encouraging participants to share both positive and negative experiences, and cultivating longitudinal relationships to encourage candor [100–102]. Second, clinical outcomes data will be derived from the EHR, which is known to have high rates of missing or misclassification of socially assigned race. Although this is concerning, 1) evidence indicates that EHR-based clinical data provides more objective estimates than claims-based data for sepsis surveillance [4], 2) any bias is likely toward the null (as most errors are of identifying LatinX patients as NHW) [103–105] and 3) there is no alternative. Further, we anticipate that some sites may use this project as an opportunity to highlight and correct for historical underinvestment in systematic, reliable capture of socially assigned race and other important demographics in their EHR. Third, Coalition turnover is expected to occur, limiting paired analyses of quantitative data. However, our prior research found that neither coalition size nor turnover was associated with intervention outcomes [30] (an association that we will evaluate in the proposed study as well). Further, organizations that were more successful in driving changes in organizational culture were observed to proactively adjust their coalition membership to adapt to changes in organizational leadership, to engage emerging champions, and to account for the specific aspects of AMI care they were addressing. Additionally, our study is designed to measure systems-level (rather than individual-level) phenomena, and we anticipate that the roles represented on the coalitions will remain relatively stable even as individuals come and go. Fourth, as with all health interventions there is a lag in time between implementation of practice change and corresponding adjustments in outcome rates. Subsequently, we plan to track difference in AA/B and NHW patients and LatinX and NHW patients for each of our clinical outcomes for 2.5 years post intervention implementing different lag periods (up to 6 months of lag time between the end of the intervention and time of observed clinical outcomes). Fifth, we may face limitations in attributing observed changes to the intervention. Hospitals will be exposed to multiple sources of knowledge during the intervention and may also undergo substantial internal shifts in staff and priorities. The mixed methods design of the proposed study is expected to allow us to capture and understand factors beyond the intervention that may be influencing the results.

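### The Aim 2 survey model cannot separate intervention effect from change over time, yet its result is reported as impact and labels systems as having responded to the intervention

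*Protocol article*

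**What the plan says.** Aim 2 is introduced as an evaluation of the intervention's impact on organizational culture. Under Survey, about 15 coalition members in each of eight systems ("8 x ~ 15 members = 120") are surveyed at launch, midpoint and end. The model will "estimate the association between mean scores and time, accounting for clustering of individual respondents within systems". The testing rule is "We will use statistical analysis to determine significant changes at the level *p* < 0.05", applied "for overall culture and each of the 4 domains for each system and the full sample". The section then says the survey serves to assess the impact of the intervention.

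The integration paragraph (end of the Data collection section) classes a site as positive change if it meets either of two criteria. The quantitative one is "statistically significant change in overall readiness score from baseline to follow up". The qualitative one is a marked, consistent shift across three to four domains with little disconfirming evidence.

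Aim 3 (Analytic approach) stratifies the interrupted time series by this label and compares "changers (systems that responded to the intervention) and non-changers, health systems that did not respond to the intervention".

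The Discussion concedes that attribution may be limited: "Hospitals will be exposed to multiple sources of knowledge during the intervention and may also undergo substantial internal shifts in staff and priorities". It relies on the mixed methods design to understand such factors.

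**The concern.** Every surveyed system is exposed over the same period. There is no comparison system and no survey series before launch, so calendar change and intervention effect are one coefficient. Covariates added in a fuller plan would not separate them.

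Two statements go further than this design allows. The full-sample time effect is called impact of the intervention, although any common drift in scores would make it significant. A system whose score moved significantly from its own baseline is then said to have responded to the intervention. Because either criterion suffices, the qualitative evidence can add a changed system but cannot remove one that the survey created. At stake is what Aim 2 can claim, and how a difference between groups in Aim 3 may be described.

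**Working it through.** **The plan's own figure.** 8 × 15 = 120, which agrees with the stated survey sample. The article gives no SD, effect size, drift or within-person correlation for the survey, so nothing else can be reproduced.

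**Assumptions.** 15 respondents per system at launch and at end; scores in SD units; no intervention response in any system; the same upward drift d in all eight; within-person correlation ρ = 0 (unpaired), 0.3, 0.5 or 0.7; two-sided 0.05 (the protocol does not state sidedness). The quantitative criterion gives no direction; only upward results are counted as positive change.

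**Formulas.**
- Standard error of one system's change: √(2(1−ρ)/15). Unpaired: √(2/15) = 0.365, 28 df. ρ = 0.5: √(1/15) = 0.258, 14 df. ρ = 0.7: √(0.6/15) = 0.200, 14 df.
- Full-sample test: a t-test on the eight system mean changes, standard error as above divided by √8 (0.129, 0.091, 0.071), 7 df.
- Example: d = 0.5, unpaired. Noncentrality per system is 0.5/0.365 = 1.37, which gives 26%. For the full sample it is 0.5/0.129 = 3.87, which gives 91%.

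Results from 20,000 simulated replicates, in agreement with the noncentral t values where these were computed:

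| Drift | ρ | False positive change per system | Expected systems of 8 | Full-sample rejection |
|---|---|---|---|---|
| 0.25 SD | 0 (unpaired) | 10% | 0.8 | 39% |
| 0.25 SD | 0.3 | 12% | 0.9 | 52% |
| 0.25 SD | 0.5 | 15% | 1.2 | 65% |
| 0.25 SD | 0.7 | 21% | 1.7 | 86% |
| 0.5 SD | 0 (unpaired) | 26% | 2.1 | 91% |
| 0.5 SD | 0.3 | 33% | 2.7 | 98% |
| 0.5 SD | 0.5 | 44% | 3.5 | over 99% |
| 0.5 SD | 0.7 | 64% | 5.1 | over 99% |

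With no drift the per-system upward rate is 2.5% and the full-sample test holds 5%.

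**Sensitivity to uniform drift.** If drift itself varies between systems with an assumed SD of 0.3, full-sample rejection at 0.25 SD mean drift falls to about 26% (unpaired) or 34% (ρ = 0.5).

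**Consequence for Aim 3.** Let four systems truly respond by 1 SD and four not at all. The difference in mean true response between systems marked as changed and the rest is:

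| Drift | Unpaired | ρ = 0.5 |
|---|---|---|
| 0 | 0.80 | 0.94 |
| 0.25 SD | 0.84 | 0.89 |
| 0.5 SD | 0.79 | 0.72 |
| 0.75 SD | 0.69 | 0.61 |

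At 0.75 SD drift all eight systems fall in one group in about 7% of replicates unpaired and 35% at ρ = 0.5.

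**Relative change.** Testing each system against the mean change of the other seven keeps false positive change near 2.5% per system at every drift value.

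**The case against.** The strongest reply has four parts.

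- **The classification fits the hypothesis.** The Background hypothesis concerns hospitals whose culture improves, whatever the cause. A system whose culture truly rose is then correctly placed, and only the parenthetical wording in the Analytic approach overreaches. This stands. It is why the remedy is mainly one of wording and the planned split can stay.
- **Shared upward drift is not predicted.** A reader might infer from "given the well-document impact of the pandemic in exposing structural racism and exacerbating racial inequities" that the protocol expects scores to rise everywhere. It does not say so. That clause argues that the study is timely, and the same paragraph expects COVID-19 to strain organizations' capacity for change, which could lower scores. The staff and priority shifts in the limitations are specific to each hospital. Sign, size and uniformity of drift are therefore assumptions.
- **The larger figures need pairing.** The limitations expect turnover to restrict paired analyses, so the unpaired rows may be nearer the truth. This also stands. A reader might infer that Aim 3 is badly diluted, but unpaired the contrast barely moves up to 0.5 SD drift.
- **Attribution limits are disclosed, and the time series handles secular trend.** Only partly. The disclosure is general and changes no label, and the ten pre-intervention quarters address trend in clinical outcomes, not in culture scores.

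It is also tempting to replace the split with a continuous score, whose correlation with true response at ρ = 0.5 stays at 0.91 at every drift value. That is a correlation and cannot be compared with the retained differences above. Replacement would also drop the qualitative criterion and remove any true effect common to all systems.

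**Conclusion.** The concern holds as a limit on attribution. The survey has no comparator and no pre-launch series, so its time effect shows change over the intervention period and cannot by itself show impact. Nor does a significant change from a system's own baseline show that the system responded to the intervention.

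How often this would mislead depends on drift that the protocol does not quantify. Under the uniform upward drift assumed above, even the unpaired case gives about one system in ten falsely marked at 0.25 SD and one in four at 0.5 SD. The full-sample test is the more exposed of the two.

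The documents do not support a claim that false changers will be common, or that the Aim 3 comparison is seriously compromised. Material dilution needs large drift or strongly paired responses.

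**What to change.** 1. **Wording.** In the Aim 2 introduction and the Survey section, report the full-sample time effect as change over the intervention period among participating coalitions, not as impact of the intervention. In the Analytic approach, define the groups as systems whose culture did or did not improve, which matches the Background hypothesis.
2. **Sensitivity analysis.** Keep the mixed-methods split as planned. Add an Aim 3 analysis with each system's change in overall culture score, as a deviation from the eight-system mean, as a continuous moderator of the change in racial gap.

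The cost is slightly more analysis and a weaker claim; no new sites, patients or survey waves are needed. The moderator measures relative change only, cancels only drift shared by all eight systems, and does not use the qualitative criterion. Separating a common intervention effect from common drift would need culture measured in systems without the intervention or over a pre-launch series, which this design does not have.

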#### Interviews and observations

In-depth, in-person interviews will be conducted by trained members of the research team with different disciplinary backgrounds, using a standard interview guide (Additional File 4)**,** beginning with a grand tour question [76]: “*Tell me about your experiences in working to address racial inequities in sepsis care*,” with structured probes to encourage participants to describe specific examples or vignettes. The sample will include Guiding Coalition members and additional key informants [56] as needed to achieve thematic saturation [77] at each site. As is typical with in-depth interviewing [78], we anticipate interviews will be approximately 1 h in length. Interviews will be audiotaped and transcribed by independent, professional transcriptionists to enhance data reliability. At each site, we will also observe 2–8 h of daily routines in relevant community and hospital settings tailored to the sepsis project at each site.

#### Data collection

Observations will be completed by an experienced researcher using a standard observation template (Additional File 5) [79, 80] including context, stakeholders, and events, synthesized as field notes at the completion of the site visit. Intervention teams will participate in a debriefing session immediately upon return from site visits; reflections will be included in the qualitative data set for analysis. *Analysis:* Transcribed interview and ethnographic data will be analyzed by a 5-person multidisciplinary team using the constant comparative method of qualitative data analysis [81]. Coding of the data will include a series of iterative steps, beginning with an initial ‘start list’ of codes [82] to be refined during analysis of transcripts from subsequent interviews. We will conduct iterative coding and analysis with each wave of data collection, using negotiated consensus to resolve differences in interpretation, until a final code structure is established [82]. We will implement longitudinal analysis using matrices (rows = single case, group or theme, columns = time) to uncover patterns and interrelationships in change over time within and across health systems [83]. Data will be entered into ATLAS.ti to facilitate analysis. We will systematically search for disconfirming evidence [84], interview multiple participants in each health system for triangulation [85], and maintain a detailed audit trail to document analytic decisions [76]. To our knowledge, this will be one of the largest longitudinal qualitative data sets in the country [83], and could support sub-investigations on the nature of structural racism and health [31, 86].

Integration will be accomplished through merging in a mixed methods matrix [69, 87] at the final stage of analysis (Additional File: 1 Supplemental Fig. 4). For each site, we will integrate quantitative trend data (overall and by each domain of the survey) and qualitative data. We will classify each site as having positive or no change based on meeting either quantitative (statistically significant change in overall readiness score from baseline to follow up) or qualitative criteria (marked shift in culture characterized by substantial, consistent, specific illustrations of notable changes in three to four of the domains of culture and little to no disconfirming evidence). We will use comparative analysis to describe differences between the systems that achieve substantial change and those that do not. Finally, we will examine differences in clinical outcomes as described in Aim 3 below. Note: analysts will be blinded to all clinical outcomes data during this analysis.

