#### Linking from underlying racism to clinical outcomes

The conceptual model below (Fig. 1), which we developed based on synthesis of existing evidence on race-based inequities in healthcare and outcomes, shows how racism is manifest across the sepsis care continuum, and provides a starting point for our work to measure and intervene on the domains of organizational culture that are required to mitigate structural racism [8, 14, 47–50]. At the foundational levels of the framework are ecological barriers to health equity, factors that are deeply embedded in our US society that perpetuate structural racism [51]. Through facilitated collaboration, Guiding Coalitions will increase their home systems’ attention to these factors. The next level defines domains of organizational culture associated with organizational capacity to mitigate structural racism. These domains, derived from our own work in organizational culture change and consistent with capacity for whole systems transformation, are the capacities that will be strengthened through the proposed intervention [27, 29, 30, 32]. The next level defines ways in which structural racism impacts the sepsis care pathway, moving from risk and primary prevention on the left to standards-based follow up care on the right. Participating sites will use their own data to name and prioritize the inequities most salient in their own systems and apply a proven strategic problem-solving process [52] to understand and address these symptoms of structural racism. Finally, at the highest level, we will measure the impact of these changes on racial inequities in care and outcomes for patients with sepsis.

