#### Intervention components

Based on our prior success in similar organizational change efforts [29], the 2.5 year intervention will include three components: 1) a series of five semiannual virtual, cross-site forums attended by four key members of each Guiding Coalition; 2) a series of four one-day workshops onsite with the full coalition at each hospital; and 3) a web-based platform to allow sites to share experiences and to serve as a repository for program resources. The content will build on and extend the previously published LSL curriculum [29]. *Semiannual forums* will bring sites together as a learning community for advice and problem solving on culture change to address structural racism in sepsis care. The sequence of forums will move sites from understanding and ‘buying in’ to the evidence base to sharing implementation challenges and successes. In the annual and closing forums, sites will vote for the “STAR” (Striving to Achieve the Remarkable) site that best exemplifies commitment to the objectives of the learning community, a highly motivational activity in LSL. *On site workshops* will build leadership capacity within the full Guiding Coalition to mitigate structural racism as it manifests in sepsis care. Each of the four workshops will include one full day of content, scheduled based on site preferences. The core curriculum for the workshops will incude both *how to work* (improving the domains of organizational culture that are required to mitigate structural racism and the underlying ecological barriers to health equity) and *what to work on* (strategic problem solving [52] to address root causes of inequities in sepsis care and outcomes in their site, see Additional File 1; Supplemental Fig. 2 for examples). In the first workshop, we will orient Guiding Coalition members to the intervention and the evidence base, promote reflection on their own measures of inequities in sepsis care and baseline organizational culture (survey measure described below), and name a problem statement and objective on which the group will focus their root cause analysis process. We will also invest in effective working relationships and processes among coalition members, including representation and role clarity [58], decision-making [59], and accountability [60]. Between workshops, the coalitions will be tasked with making and measuring progress toward addressing identified priority root causes of racial inequities in sepsis care in their home systems. At subsequent workshops, members will report on their progress, with the goal of solving implementation challenges and further developing their individual and group capacity for adaptive leadership [25, 26]. Additional workshop content will include diagnosing and shaping organizational culture, engaging conflict productively [61], using levels of analysis to diagnose organizational challenges [62, 63], and working with power and hierarchy [64, 65]. Content will be tailored to the local context by adjusting the timing of these modules to meet teams’ most pressing needs, adapting the specific examples and experiential learning exercises used in each module, articulating linkages between these content areas and ongoing work in each site, and encouraging each site to focus on root causes of inequities in sepsis care and treatment that are most salient in their environment. The facilitation team will include expert facilitators from across the United States, with backgrounds in organizational development, leadership education, anti-racist organizational change, and clinical quality improvement; most facilitators will be drawn from a faculty pool with deep experience developed through prior successful projects. Facilitators will work in teams of two or three, including a lead facilitator and additional experts tailored to the needs of each site. To promote standardization across sites while allowing for adaptation to local context, facilitators will use a fidelity checklist for each workshop. At the end of each workshop, the lead facilitator will prepare a structured written summary of decisions and action items for report back to the Guiding Coalition and to the full facilitation team. Between workshops, *a web-based information sharing platform* will serve two primary functions: (1) to serve as an accessible, up-to-date repository of project materials and references and (2) to support direct communication across hospital teams for sharing of successes, barriers, and project updates.

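### The blind on changer classification is incomplete: coded interviews and intervention-team debriefs can bring outcome information to the analysts who set the label used in Aim 3

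*Protocol article*

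**What the plan says.** The blinding statement is in the integration paragraph that closes the Aim 2 part of the protocol article, after Data collection: "Note: analysts will be blinded to all clinical outcomes data during this analysis". It has no qualification.

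The same paragraph gives the rule for the label: "We will classify each site as having positive or no change based on meeting either quantitative" or qualitative criteria. The quantitative route is a significant change in the overall survey score. The qualitative route is a "marked shift in culture characterized by substantial, consistent, specific illustrations of notable changes in three to four of the domains of culture", with almost no evidence pointing the other way. Either route is enough.

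Three kinds of material feed the qualitative route:

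- **Interviews.** "The sample will include Guiding Coalition members and additional key informants". The opening prompt is "Tell me about your experiences in working to address racial inequities in sepsis care", followed by probes for specific examples.
- **Observation field notes** from each site.
- **Debriefs.** "Intervention teams will participate in a debriefing session immediately upon return from site visits; reflections will be included in the qualitative data set for analysis".

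On what the informants know, the conceptual-model section says: "Participating sites will use their own data to name and prioritize the inequities most salient in their own systems". Under Intervention components, the first workshop has members consider their own inequity measures. Coalitions then measure progress on their chosen root causes between workshops, and "At subsequent workshops, members will report on their progress, with the goal of solving implementation challenges".

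The Analytic approach section for Aim 3 makes changers versus non-changers the comparison in the interrupted time series.

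**The concern.** The blind is there to prevent circularity: a label that will be used to compare outcomes should not be influenced by those outcomes. Holding back the outcome data set achieves this only if the coded material is itself free of outcome information. Here that material comes from people who are not blind, namely coalition members working from local data and intervention teams returning from site visits.

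If a site says that its gap has narrowed, a coder may more readily see a marked culture shift there; a site that says the opposite supplies disconfirming evidence. The label would then be associated with the outcome even if culture had no effect on it. The error has a direction: it favours the hypothesis that sites whose culture improved reduced inequities more. With eight sites, one or two labels affected in this way could matter.

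**Working it through.** The plan states no figure on this point, so there is none to reproduce. The check is mainly a trace through the text.

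**Step 1. What is withheld.** The blind refers to clinical outcomes data. Read naturally, that is the quarterly record-based series on antibiotic time, in-hospital mortality and readmission described under Aim 3.

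**Step 2. What is coded.** Interview transcripts, ethnographic notes and intervention-team debrief reflections. The article describes no removal of outcome statements from them.

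**Step 3. What the sources know.** Coalition members see their site's inequity measures from the first workshop and measure progress afterwards. Intervention teams debrief immediately after site visits. Both groups can hold outcome-related information, and both supply coded text.

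**Step 4. Whether timing allows leakage.** The intervention lasts 2.5 years. The Analytic approach section sets the post-exposure period as the 10 quarters from its start. Informants in later waves can therefore speak about quarters that Aim 3 analyses.

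**Step 5. Whether leakage can reach the label.** Yes. The qualitative route is a judgement and is sufficient by itself. The survey route is a significance test and does not depend on what the coders know.

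**Step 6. Illustration of the consequence (assumptions, not figures from the plan).** Take eight sites with no true link between culture C and outcome improvement Y, both standard normal. Let the label score be S = r·Y + √(1 − r²)·C, and call the top 4 or top 5 sites changers. Compare Y between groups with a two-sample t-test at two-sided 0.05, over 40,000 runs. The correlation r stands for leakage alone.

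| r | Mean difference, between-site SD (4/4; 5/3 split) | Significant in favour of changers (4/4; 5/3 split) |
|---|---|---|
| 0 | 0.00; 0.00 | 2.6%; 2.5% |
| 0.2 | 0.29; 0.29 | 5.5%; 5.3% |
| 0.3 | 0.43; 0.44 | 7.6%; 7.4% |
| 0.5 | 0.72; 0.73 | 14.8%; 14.1% |
| 0.7 | 1.02; 1.03 | 29.0%; 27.6% |

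The mean differences can be checked by hand. Because E[Y | S] = r·S, the difference is proportional to r. For the 4/4 split the multiplier is 0.29 / 0.2 = 1.45, which gives 1.45 × 0.5 = 0.725 and 1.45 × 0.7 = 1.015, in line with the table.

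**The case against.** The case on the other side is substantial, and much of it stands.

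- **A reader might infer that the blind cannot hold, or that the coded text is bound to contain the Aim 3 results.** The documents do not say so. Coalitions track locally chosen root causes, which need not be the three Aim 3 outcomes. The first workshop shows a starting level, not a change. The interview prompt asks about experiences, not results. Withholding the outcome series is a real safeguard.
- **A reader might also infer that workshop progress reports are coded.** They are not listed as coded data, and the lead facilitator's written summary goes to the coalition and the facilitation team. Such reports reach the coders only indirectly, through interviews and debriefs.
- **The qualitative bar is high.** It needs consistent, specific illustrations across three to four domains, and the coding uses consensus, several informants per site, a search for contrary evidence and an audit trail. One remark about a metric would not meet it. These steps make the coding more reliable, but they do not remove outcome knowledge shared by several informants at a site.
- **The article is condensed, and the interview guide and observation template are in additional files.** Transcript handling may be described elsewhere, and its absence here is not the point. The point rests on what the article does state: an unqualified blind, debriefs placed in the coded data set, and a judgement that suffices for the label.
- **The simulation is not the planned analysis.** It ranks sites and fixes a split, applies r to the whole label although a site may qualify on the survey alone, and uses a site-level t-test where the plan has segmented mixed-effects regression. All of this is correct, so its percentages cannot be read as error rates for this study.

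**Conclusion.** The concern holds in a limited form. The blind is real but incomplete. It covers the Aim 3 outcome series, but as the plan is written it does not stop outcome information from reaching the coders through interviews with informed coalition members or through intervention-team debriefs. Since the qualitative criterion alone can make a site a changer, and the label defines the Aim 3 groups, any such leakage would bias the contrast towards an apparent benefit of culture change.

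The size is unknown. The documents give no basis for a value of r, and r could be close to zero. The simulation shows only the direction, and that a modest assumed correlation of 0.2 to 0.3 would double or triple the chance of a false finding favouring changers in that simplified setting. The conclusion rests on two assumptions: that some informants or intervention-team members mention outcome results, and that coders are influenced by them. Both are plausible; neither is established by the text.

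**What to change.** Amend the integration paragraph of Aim 2 as follows:

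1. Exclude intervention-team debrief reflections from the evidence used to classify sites, and keep them for the analysis of mechanisms.
2. Where feasible, mask explicit statements of antibiotic-time, mortality or readmission results in transcripts and field notes before coding for classification. The independent transcription already planned is a natural place for this. Masking will not remove a generally success-coloured account, so it reduces the problem without ending it.
3. Date-stamp and lock all eight labels before any intervention-period Aim 3 results are released to the classifying analysts. Extraction by other staff need not wait.
4. Reword the blind to say that the Aim 3 outcome series is withheld, and to name whatever else is masked.
5. Add a sensitivity analysis of the Aim 3 contrast with sites classified on the survey criterion alone. State its limit: survey respondents are coalition members who may also know their site's results, so it removes the coders' judgement but not the respondents' knowledge.

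The cost is protocol wording, a modest masking step and one further analysis. The downside is slightly less qualitative material behind each label.
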